#### 2.9.4. Secondary Analyses

Direct associations of temperature, humidity, and pollutants with health endpoints during walking will be evaluated using additional mixed-effects models. Exposure metrics will be averaged over defined time intervals, and endpoint changes will be estimated as percent differences.

#### 2.9.5. Exploratory Neighborhood-Level Analyses

Time series data from site monitors and regional models will be used to assess the broader impact of the microforest on local climatic conditions. Two reference groups will be used: (1) Founders Square pre-intervention and (2) the adjacent parking lot. Interrupted time series regression will estimate intervention effects, with the planting date as the interruption point. Weekly aggregated data will be analyzed, and Fourier terms will capture seasonal variation. Future analyses may also explore changes in human mobility patterns, using cluster analysis of objective measures (e.g., GPS or cellular trace data) to identify microforest features most associated with increased visitation. We will use an interrupted time series analysis to evaluate the effectiveness of the microforest intervention on lowering regional temperatures and pollution levels [60]. The interrupted time point will be defined as the date of the microforest planting. Time series data will be aggregated to weekly values pre- and post-intervention for analysis. We will fit Fourier terms in our model to capture seasonal patterns in our data [61]. In future exploratory analyses, we could also consider examining the effect of specific aspects of the greening intervention on human mobility patterns. We will use cluster analysis to identify the specific characteristics of the microforest and its environment that are most strongly associated with changes in human mobility patterns. We can use objective measures of mobility, such as GPS tracking or cellular phone traces, to determine the frequency and duration of visits to different types of green spaces. This analysis will help us to better understand the mechanisms underlying the relationship between green space and health [62,63].

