### 2.3. Environmental Data Collection

#### 2.3.1. Meteorological Monitoring

To capture meteorological conditions, we deployed two types of weather stations: a WiFi-based “prosumer” system (Tempest Weather Station, WeatherFlow Inc., Santa Cruz, CA, USA) and a research-grade system (Campbell Scientific Inc., Logan, UT, USA). The Tempest stations record a wide range of variables (Table 2) at 1 min intervals and automatically transmit data to a hub and redundantly log in cloud storage. In summer 2023, six Tempest stations were installed, four at the corners of the site and two near the center, allowing measurements across varied shade and ground-cover conditions.

To ensure accuracy and provide long-term monitoring, a Campbell Scientific research-grade station was installed at the site’s center. This station records many of the same meteorological variables as the Tempest, but its temperature sensor is housed in a fan-aspirated shield to prevent stagnation bias. Data are recorded at 1 min intervals and manually downloaded from the datalogger. A fine temporal resolution is used, corresponding to participant exposure periods as part of the human crossover component. Site-wide microclimatic analysis will use hourly and daily data, which can be aggregated into monthly datasets for long-term analysis. Both the Tempest and Campbell systems collected baseline data until site construction began. The central research station and two Tempest units were removed for construction; the research station was reinstalled in December 2024, while the central Tempest stations were permanently eliminated from the final design (Supplemental Figure S1).

During the second round of clinical trials, before the Campbell station was reestablished, a mobile cart system was developed to replicate the fixed-station measurements. This was done to ensure continuity of meteorological measurements when the central fixed station had to be removed during construction. The mobile unit collected equivalent variables at 1 min intervals and was activated at least 30 min before participant arrival to ensure stabilization. In parallel, one researcher wore an AirBeam3 device during participant walks, providing second-by-second measurements of particulate matter (PM_1_, PM_2.5_, and PM_10_).

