#### 2.3.2. Spatial Characterization of Vegetation Structure (LiDAR)

LiDAR scans have been and will continue to be acquired periodically as the microforest gets established. An initial LiDAR scan was performed in August 2022 utilizing a drone (Figure 2). This was followed by a scan in January 2023, prior to construction, and another in May 2024 during construction. The last two scans utilized a backpack LiDAR device to more effectively capture vegetation density, which will also be used for future scans. The LiDAR data will allow for the structural characterization of vegetation density, canopy development, and quantification of three-dimensional vegetation before and after intervention.

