### 2.8. Greening Intervention: The [name] Microforest

#### 2.8.1. Site Preparation and Infrastructure

The intervention began after completion of the first round of baseline testing in Summer 2023. Initial site modifications included the removal of the existing central walkway and the installation of a semi-circular retaining wall, along with a new perimeter walking path (Figure 5). The retaining wall is three feet tall and spans 188 feet, and the wall’s thickness varies from one to two feet to support the weight of the new soil. Benches and lighting were added, and the retaining wall was backfilled with approximately 700 tons of Nugent soil to create a three-foot raised area sloping southward. In addition, metal signage and fins were installed on the south side of the retaining wall to complete the circle, with the signage being 66 inches in height and four inches thick, and the metal fins being 60 inches in height and one inch thick (Supplemental Figure S2). This middle well zone was planted with grass, and mulch was applied along the park’s edges prior to the wave 2 physiological assessment in Summer 2024.

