#### 2.8.2. Planting Design and Species Composition:

The primary phase of greening occurred in Winter 2024 and extended into the following months. A total of 119 trees representing 31 species were planted (Supplementary Table S2), comprising a mix of deciduous (primarily Anacardiaceae, Fabaceae, and Fagaceae families) and evergreen species (mainly Pinaceae). This combination was selected to maximize cooling benefits in a temperate climate and enhance year-round canopy cover. In addition, 242 shrubs and hundreds of herbaceous groundcover plants were installed across the site (Supplementary Table S3). Plant material was sourced from nurseries in multiple states and transported directly to Louisville to minimize storage stress prior to planting.

Trees were planted in close spacing (1–1.5 m apart) to accelerate canopy closure. Shrubs were positioned between rows to form a layered understory, while herbaceous species and groundcovers filled interstitial spaces. This stratified planting scheme was designed to mimic natural forest succession, increase soil infiltration, suppress weeds, and promote early biodiversity. Collectively, these dense plantings are expected to enhance evapotranspirative cooling, mitigate urban heat, and improve ecosystem resilience (Figure 6A,B). Progress of installation is shown in Figure S3.

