#### 2.9.6. Environmental Data Analysis

Meteorological data from the Tempest and Campbell Scientific stations will be quality-controlled to identify and correct erroneous or missing values. Data will be averaged over 15 min intervals for analysis. Two primary analyses are planned: (1) Intra-park analysis—hourly park-wide temperature averages on synoptically stable days (clear skies and calm conditions) will be compared across stations to identify spatial variability due to shading, ventilation, and ground cover. Anomalies relative to park-wide averages will be correlated with solar radiation, wind speed, and ground cover type; and (2) Post-intervention analysis—post-planting data will be compared with baseline measurements to quantify immediate and long-term microclimate effects of the intervention. Long-term trends will be assessed using the central Campbell Scientific station, with monthly statistics computed for all variables. Data will be compared with other stations in the University of Louisville network and with National Weather Service stations to evaluate the microforest’s contribution to reducing the urban heat island effect. Statistical comparisons will use nonparametric tests (e.g., Wilcoxon rank-sum), with significance defined as *p* < 0.05.

Biological and Ecological Data Analysis Avian data will be analyzed in RStudio (v4.3.1) to compare species abundance and diversity across sites ([name] Microforest, University Quad, Nettleroth Sanctuary). Microsoft Excel will support visualization. Surveys will continue after planting to assess temporal changes in avian presence.

Soil flux data (CO_2_ and CH_4_) will be analyzed using multiple linear regression models, with explanatory variables, including vegetation presence, soil moisture, soil temperature, and photosynthetically active radiation (PAR). Variables showing multicollinearity (r ≥ 0.60) will not be included in the same model. Candidate models will be evaluated using Akaike’s Information Criterion corrected for small sample size (AICc), with models within ΔAICc < 2 considered equivalent.

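### The interrupted time series in section 2.9.5 has at most about one undisturbed year of site data before planting, and no pre-planting series is described at its parking-lot reference, so year-to-year weather and construction can mix with the planting effect

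*Protocol article*

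**What the plan says.** Section 2.9.5 fixes the main elements of the analysis. The method is interrupted time series regression, the interruption is the planting date, and "Weekly aggregated data will be analyzed, and Fourier terms will capture seasonal variation". On comparators it states: "Two reference groups will be used: (1) Founders Square pre-intervention and (2) the adjacent parking lot". Regional models are mentioned as a data source, without a stated role as control.

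Other sections show what those references contain:

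- Section 2.3.1, start of recording: "In summer 2023, six Tempest stations were installed, four at the corners of the site and two near the center". On its end: "Both the Tempest and Campbell systems collected baseline data until site construction began". The central research station and two Tempest units were taken out for construction. The research station came back in December 2024, and the two central Tempest units did not return.
- Section 2.8.1: "The intervention began after completion of the first round of baseline testing in Summer 2023". The works listed before Wave 2 are a new perimeter path, a retaining wall, about 700 tons of soil, grass and mulch.
- Section 2.3.2 dates a LiDAR scan as "another in May 2024 during construction".
- Section 2.8.2 places the main planting in Winter 2024 and the months after it, "comprising a mix of deciduous (primarily Anacardiaceae, Fabaceae, and Fagaceae families) and evergreen species (mainly Pinaceae").
- Section 2.3.1 speaks of concurrent measurement at the site and the parking lot in the future tense only.
- Section 2.9.6, as part of a separate analysis that gives a rank-sum test as its example: "Data will be compared with other stations in the University of Louisville network and with National Weather Service stations".

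**The concern.** A pre/post step in temperature can be read as an effect of planting only if nothing else differs systematically between the two segments, or if a concurrent control carries the other differences. Two other things differ here. The undisturbed baseline falls in one particular year, while the post-planting segment falls in later years. Fourier terms describe the average annual cycle and cannot absorb a warm or cool year. In addition, the site was rebuilt between the undisturbed baseline and planting, so part of the pre-planting segment already reflects new ground cover, a raised soil bed and a reduced set of stations.

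Neither named reference is shown to solve this. The square before intervention is the series with the problem. A lot first monitored after planting gives a contrast between sites, not a change from before to after.

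At stake is the Aim 3 hypothesis that the microforest lowers heat and pollution, which the article hopes will inform urban policy.

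**Working it through.** The article gives no series length, power or precision for this analysis, so there is no stated figure to reproduce.

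**Step 1. Undisturbed site record (date arithmetic).** Exact dates are not given, so ranges are used.
- Longest case, works starting in May 2024: 1 June 2023 to 31 May 2024 is 365/7 = 52.1 weeks; 21 June 2023 to 1 May 2024 is 315/7 = 45.0 weeks.
- Shortest case, works starting by 22 September 2023: from 31 August, 22/7 = 3.1 weeks; from 1 June, 113/7 = 16.1 weeks.

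The undisturbed record is therefore about 3 to 52 weeks, at most about one annual cycle.

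**Step 2. Whole pre-planting segment.** Taking Winter 2024 as December 2024:
- 31 August 2023 to 1 December 2024 is 458/7 = 65.4 weeks.
- 1 June 2023 to 31 December 2024 is 579/7 = 82.7 weeks.
- If planting is dated to 28 February 2025, the upper limit is 638/7 = 91.1 weeks.

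Even with the latest start of works (31 May 2024) and the earliest planting date (1 December 2024), 184/7 = 26.3 weeks of this segment come after works had begun.

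**Step 3. What the step estimate absorbs.** The fitted model was y = a + b·post + two sine/cosine pairs of annual period + error, on weekly data, with HAC standard errors (lag 6). The true effect was zero, with 600 replicates per scenario. None of the following comes from the documents; all are assumptions:
- year-to-year SD 0.3, 0.6 or 0.9 °C
- weekly SD 2 °C with autocorrelation 0.3
- independent noise of 0.3 °C in the site and in the reference
- 130 post-planting weeks
- a reference that shares all regional weather with the site
- no construction effect.

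Each cell gives the false-positive rate at nominal 5%, then the SD of b.

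| Pre-segment | Series | Year SD 0.3 °C | 0.6 °C | 0.9 °C |
|---|---|---|---|---|
| 40 weeks, works dropped | site alone | 17%, 0.59 °C | 26%, 0.74 °C | 37%, 1.06 °C |
| 78 weeks to planting | site alone | 15%, 0.48 °C | 28%, 0.68 °C | 40%, 0.92 °C |
| 40 weeks, works dropped | site minus reference | 12%, 0.08 °C | 12%, 0.08 °C | 12%, 0.08 °C |
| 78 weeks to planting | site minus reference | 7%, 0.06 °C | 7%, 0.06 °C | 8%, 0.06 °C |

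Extending the pre-segment from 40 to 78 weeks does not remove the problem; differencing does. The 7-12% that remains no longer depends on the year SD and reflects HAC standard errors in short series, so some of the 15-40% has that source too. As a yardstick, the Introduction cites 0.4 °C as the estimated summer benefit of 30% tree cover across 93 European cities. Every site-alone SD exceeds it.

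**Step 4. Season, if one constant step is fitted.** Assume a true cooling of 0.4 °C in 28 leaf-on weeks of 52 and none otherwise. The plain average is 0.4 × 28/52 = 0.22 °C. The simulated step, in the differenced series (300 replicates), was 0.21 °C with 40 pre-weeks and 0.24 °C with 78, or 53% and 60% of the summer value. The dilution depends on the baseline. With only 20 pre-weeks, starting in June, and a true leaf-on effect of -1.0 °C, a noise-free fit gave -0.89 to -0.99 °C, so hardly any dilution.

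**The case against.** The strongest reply is that the plan does have concurrent comparators. The lot is named in the same paragraph, regional models are a listed data source, and section 2.9.6 brings in network and National Weather Service stations. Any concurrent control cancels shared year effects, as the table shows. This stands in principle. It fails on what is described. Every fixed station described for the baseline stood in Founders Square, and monitoring on summer visit mornings is not a weekly series. The outside stations belong to a different analysis, and the regional models have no stated control role. How the lot enters the regression is also not said, but that alone could be left to a fuller plan.

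Four stronger readings are tempting, and the documents do not support them:

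- A reader might infer that the planned pre-segment is shorter than a year. It is not: the stated interruption is planting, so the segment is about 65-83 weeks. The difficulty is that it mixes undisturbed baseline with works. Only two of the six Tempest units are reported as removed, so some site recording may have continued.
- A reader might infer Fourier terms shared by both periods and a single constant step. The article does not say, and a condensed text may leave this out, so the dilution in Step 4 is conditional.
- A reader might call the planting largely deciduous. The article describes a mix, chosen partly for canopy cover throughout the year.
- A reader might think the heat-buffering argument for Aims 1 and 5 depends on this model. It does not. Aim 1 is a within-person randomized site comparison, and exposure differences come from personal and fixed or mobile monitors.

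It is also fair to say that the simulated magnitudes rest on assumed SDs.

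**Conclusion.** The point holds for the design as described. Neither reference in section 2.9.5 is shown to supply an undisturbed before-and-after control, and Fourier terms cannot separate planting from calendar year. A step estimated at the square can therefore combine planting, year-to-year weather and construction.

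For year-to-year weather alone, the size is about 15-40% false positives at nominal 5%, with a step SD of roughly 0.5-1.1 °C for assumed year SDs of 0.3-0.9 °C. The construction effect was not quantified. The improvement to 7-12% assumes a reference that follows the site's weather closely, so real stations at a distance would do less well.

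The documents do not show that the result will be wrong, only that this model could not tell. The consequence is confined to exploratory Aim 3, and the primary heart rate variability and blood pressure comparisons are unaffected. It is still worth correcting, because the needed comparators are already named one section later.

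**What to change.** In section 2.9.5:

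1. Make the outcome the weekly difference between Founders Square stations that ran throughout (apparently the corner Tempest units) and the University network and/or National Weather Service stations named in section 2.9.6. First confirm that those records reach back to 2023.
2. State the start and end of works, and treat that period as a separate phase or exclude it.
3. Use the parking lot as a pre/post control only for periods in which it was monitored. Otherwise present it as a contrast between sites after planting.
4. Let the effect differ by season, for example with Fourier-by-period terms, and report the leaf-on estimate for Aim 3.

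The cost is a change of analysis wording, a slightly more complex model and dependence on the reference stations' continuity and quality. No new measurement is needed. If the works are excluded, the pre-segment is short, and standard errors suited to short autocorrelated series should be used, since some excess false positives (about 12% with 40 weeks) remained in the simulation even after differencing.

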#### 2.9.6. Environmental Data Analysis

Meteorological data from the Tempest and Campbell Scientific stations will be quality-controlled to identify and correct erroneous or missing values. Data will be averaged over 15 min intervals for analysis. Two primary analyses are planned: (1) Intra-park analysis—hourly park-wide temperature averages on synoptically stable days (clear skies and calm conditions) will be compared across stations to identify spatial variability due to shading, ventilation, and ground cover. Anomalies relative to park-wide averages will be correlated with solar radiation, wind speed, and ground cover type; and (2) Post-intervention analysis—post-planting data will be compared with baseline measurements to quantify immediate and long-term microclimate effects of the intervention. Long-term trends will be assessed using the central Campbell Scientific station, with monthly statistics computed for all variables. Data will be compared with other stations in the University of Louisville network and with National Weather Service stations to evaluate the microforest’s contribution to reducing the urban heat island effect. Statistical comparisons will use nonparametric tests (e.g., Wilcoxon rank-sum), with significance defined as *p* < 0.05.

Biological and Ecological Data Analysis Avian data will be analyzed in RStudio (v4.3.1) to compare species abundance and diversity across sites ([name] Microforest, University Quad, Nettleroth Sanctuary). Microsoft Excel will support visualization. Surveys will continue after planting to assess temporal changes in avian presence.

Soil flux data (CO_2_ and CH_4_) will be analyzed using multiple linear regression models, with explanatory variables, including vegetation presence, soil moisture, soil temperature, and photosynthetically active radiation (PAR). Variables showing multicollinearity (r ≥ 0.60) will not be included in the same model. Candidate models will be evaluated using Akaike’s Information Criterion corrected for small sample size (AICc), with models within ΔAICc < 2 considered equivalent.

To analyze soil microbiome data, sample inference from amplicon data will first be performed using the DADA2 denoising workflow [64]. DADA2 generates amplicon sequence variant (ASV) tables, which allow for finer resolution than older OTU grouping methods [65]. Bacterial ASVs will then be annotated using the SILVA SILVA_SSU_r138_2019 database [66], and fungal ASVs will be annotated using the UNITE sh_general_release_all_10.05.2021 database [67]. Changes in microbiome community composition over time and in response to other soil properties (e.g., soil nutrients and heavy metal concentrations) will be assessed using principal components analysis. Changes in community diversity over time will be assessed using ANOVA. Indicator species analysis will be performed to identify particular microbial species associated with increased soil health factors and greenness.

Tree inventory data will be analyzed with i-Tree Eco (v6.1.47) to estimate carbon storage and sequestration, pollution removal, oxygen production, and prevented runoff. The results will be aggregated to characterize overall ecosystem services provided by the microforest.

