Both the fixed and mobile Campbell stations were calibrated following manufacturer guidelines. Parallel deployment of the Campbell and Tempest stations allowed for cross-validation during baseline measurements. Data will be acquired both at the microforest site and the impervious parking lot to obtain concurrent measurements. All data will go through quality control screening for missing values, sensor drifts, sensor faults, and anomalous spikes.

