**Figure 6 ijerph-23-00365-f006:**
[figure not shown]

[figure not shown]
Schematic of the microforest planting design. Panels depict a high-density, multilayered planting arrangement of (**A**) trees and (**B**) shrubs modeled after natural forest succession.

**Table 1 ijerph-23-00365-t001:** Summary table outlining research aims, hypotheses, and outcome measures.

Aim	Hypothesis	Exposure	Outcome Measures
Primary Aim 1	Exposure to microforest improves HRV and lowers BP vs. parking lot	Microforest vs. impervious site	heart rate variability (HRV) and blood pressure (BP)
Secondary Aim 2	Exposure to microforest improves stress responses and decreases VOC exposure	Microforest vs. impervious surface	Salivary cortisol, urinary catecholamines and their metaboiltes, urinary VOC metabolites, self-reported stress and rumination.
Exploratory Aim 3	Microforest reduces heat and pollution	Pre/post intervention; spatial monitoring, comparison with adjacent impervious surface.	Temperature, humidity, PM, NO_2_, BC
Exploratory Aim 4	Microforest enhances ecological function	Pre/post intervention	Avian diversity, microbiome composition, GHG flux, ecosystem services
Integrated Aim 5	Environmental modification mediates physiological benefits	Integrated environmental metrics	HRV, BP with environmental covariates

**Table 2 ijerph-23-00365-t002:** Meteorological variables recorded by Tempest and Campbell Scientific stations (temperature is measured with passively aspirated sensors in the Tempest stations and with fan-aspirated sensors in the Campbell Scientific station).

Variable	Tempest Stations	Research Station
Temperature (°C)	Passively Aspirated	Fan-Aspirated
Relative Humidity (%)	Passively Aspirated	Fan-Aspirated
Barometric Pressure (hPa)	√	√
Wind speed (m s^−1^)	√	√
Wind Direction (°)	√	√
Dewpoint Temperature (°C)	Calculated	Calculated
Solar Radiation (W m^−2^)	√	√

**Table 3 ijerph-23-00365-t003:** Demographic characteristics of study participants in Wave 1 (2023) and Wave 2 (2024).

	Wave 1 (2023)	Wave 2 (2024)
Age	39 [28 to 42]	42 [29 to 52]
Sex		
Male	16 (40%)	20 (40%)
Female	24 (60%)	30 (60%)
Race		
NHW	30 (75%)	28 (56%)
NHB	3 (8%)	10 (20%)
HW	0 (0%)	3 (6%)
HB	0 (0%)	0 (0%)
Other	7 (17%)	9 (18%)
Education		
≤4-year degree	21 (53%)	27 (56%)
>4-year degree	19 (47%)	22 (44%)
Income		
<$90 K	19 (47%)	27 (54%)
>$90 K	18 (45%)	21 (42%)
Declined/Don’t know	3 (8%)	2 (4%)

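### Clear-day station comparison in 2.9.6 mixes passive-shield sensor error with shading, and after construction sensor type is confounded with location

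*Protocol article*

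**What the plan says.** Section 2.3.1 describes two systems. In summer 2023, "six Tempest stations were installed, four at the corners of the site and two near the center", under varied shade and ground cover. One Campbell Scientific station stood at the centre, and "its temperature sensor is housed in a fan-aspirated shield to prevent stagnation bias". The Table 2 caption confirms the contrast: "temperature is measured with passively aspirated sensors in the Tempest stations and with fan-aspirated sensors in the Campbell Scientific station". After construction the Campbell was reinstalled in December 2024, while "the central Tempest stations were permanently eliminated from the final design".

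Section 2.9.6 sets out two analyses of data from both systems.
- **Intra-park:** "hourly park-wide temperature averages on synoptically stable days (clear skies and calm conditions) will be compared across stations to identify spatial variability". The differences are attributed to "spatial variability due to shading, ventilation, and ground cover", and "Anomalies relative to park-wide averages will be correlated with solar radiation, wind speed, and ground cover type".
- **Post-intervention:** post-planting data are compared with baseline for immediate and long-term effects. The central Campbell is named for long-term trends. No sensor is named for the immediate comparison.

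On data quality, section 2.3.1 reports that "Parallel deployment of the Campbell and Tempest stations allowed for cross-validation during baseline measurements" and plans screening for missing values, drift, faults and spikes. Section 2.9.6 adds correction of erroneous or missing values.

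**The concern.** The authors name an error to which unventilated shields are prone and remove it at one station only. They then select the conditions, strong sun and little airflow, in which a passive shield should be furthest from true air temperature. Finally they relate station differences to sun and wind, the two quantities that drive the error. A Tempest in sun will tend to read warmer than one in shade even where the air is equally warm, and the plan attributes that difference to shading.

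There is a second difficulty once the central Tempests are gone. If the Campbell enters the park-wide mean, or is compared with the corners, the only aspirated sensor is at the centre and every passive one is at a corner. Any passive bias then appears as a cooler centre, which is the direction of the Aim 3 hypothesis that the microforest reduces heat.

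**Working it through.** The plan states no figure for sensor error, so there is nothing to reproduce. Two checks show what the stated analysis would return if true air temperature were the same at every station.

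**Check 1: mixed sensor types after construction.** Inputs from section 2.3.1: six Tempests less the two central ones leaves four passive stations, plus one Campbell. Let every passive sensor read b too high and the Campbell read true.
- Park-wide mean error = 4b/5 = 0.8b.
- Centre anomaly = 0 − 0.8b = −0.8b.
- Corner anomaly = b − 0.8b = +0.2b.
- Centre minus corner = −0.8b − 0.2b = −b.

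For b = 0.2, 0.5, 1.0 and 1.5 °C, the centre looks cooler by 0.2, 0.5, 1.0 and 1.5 °C.

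**Check 2: Tempest stations only, baseline layout.** These inputs are assumptions, not document figures.
- Error = 1.5 × B × (s/900)/(1 + w), with s the local solar radiation in W/m² and w the local wind in m/s. B is the error at s = 900 and w = 0.5. B runs from 0.2 to 1.5 °C.
- Unshaded radiation is 900 sin(π(hour − 6)/13) for hours 8 to 17, over 30 days.
- The six stations receive 1, 0.3, 0.6, 0.3, 1 and 0.5 of the sun, and 1, 0.7, 1, 1, 0.8 and 0.8 of the wind.
- Clear, calm days: wind uniform on 0.3 to 1.0 m/s. Other days: wind uniform on 2 to 5 m/s, with radiation scaled by a uniform factor of 0.2 to 0.8.
- Random reading error has SD 0.1 °C.

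Simulated results with no true temperature difference:

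| B (°C) | Spread of station means, clear and calm (°C) | Spread, windier and cloudier (°C) | Correlation with solar radiation, clear and calm | Correlation, windier and cloudier |
|---|---|---|---|---|
| 0.2 | 0.11 | 0.03 | 0.39 | 0.07 |
| 0.5 | 0.28 | 0.05 | 0.69 | 0.16 |
| 1.0 | 0.57 | 0.12 | 0.82 | 0.33 |
| 1.5 | 0.83 | 0.20 | 0.85 | 0.44 |

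The spread can be confirmed by hand. The mean of s/900 at full sun is 0.776. On calm days the mean of 1/(1 + w) is 0.665 with 0.8 of the wind and 0.615 with all of it.
- Warmest station: 1.5 × 0.776 × 1 × 0.665 × B = 0.774B.
- Coolest station: 1.5 × 0.776 × 0.3 × 0.615 × B = 0.215B.
- Difference: 0.56B, which is 0.11, 0.28, 0.56 and 0.84 °C for the four values of B.
- On the windier, cloudier days the same two stations give 0.158B − 0.040B = 0.118B, so choosing clear, calm days enlarges the artefact about 0.56/0.118 = 4.7 times.

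The spurious correlation with wind speed is small in this layout (0.02 to 0.04). It is 0.09 to 0.16 with the four corner Tempests alone and 0.10 to 0.21 with the Campbell added. Solar radiation is the main problem.

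**Whether the stated safeguards reach the error.** The cross-validation was done at baseline against a single fixed Campbell at the centre, and no correction is described. The quality control looks for missing, drifting, faulty or spiking values. Shield error is smooth and plausible, so that screening is not aimed at it.

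**The case against.** The investigators plainly knew of the bias: they installed an aspirated station and ran both systems in parallel. How that comparison enters data processing is detail an article may leave to a fuller plan, and nothing says it will not be used for correction. Selecting synoptically stable days is a sound way to isolate local contrasts, bias shared by all Tempests cancels, and the hourly data are not limited to daytime. All of this stands, and it makes the point a risk rather than a certainty. It does not remove it: the article itself fixes the day selection, the attribution and the correlates, and no stated step separates sensor error from shading.

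A reader might go further and infer that Aim 3 will report planting effects, or cooling, that are instrument artefact. The documents do not support that. The intra-park analysis names shading, ventilation and ground cover, not planting. It speaks of stations and is not stated to be Tempest-only. Long-term trends use the aspirated Campbell. New shade would lower the error and new shelter would raise it, so the net sign at a retained Tempest is unknown.

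It is also tempting to set the error against the 0.4 °C quoted in the Introduction. That is an average summer reduction estimated for 93 European cities at 30% tree cover, not a within-park contrast on clear, calm days, so a ratio to it means little.

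A simple regression of Tempest minus Campbell on local sun and wind is not a clean remedy either. The two central Tempests are described as near the centre, not as co-located with the Campbell, so such a fit could remove real shade differences.

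**Conclusion.** The point holds in a limited form. As written, the intra-park analysis cannot tell a shading effect on air temperature from the part of the passive-shield error that varies with local sun. It also selects the days when that part should be largest. The spurious spread among Tempests is about 0.1 to 0.8 °C for an assumed bias of 0.2 to 1.5 °C. Those values rest on the assumed error form and station exposures, and the trial's own parallel data should replace them. The confounding after construction is exact for a uniform bias: the centre looks cooler than the corners by b. It rests on the implied four-plus-one layout and arises only if the two sensor types are pooled or compared.

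The consequence is confined to Exploratory Aim 3. The comparison of HRV and blood pressure between the two sites is not affected. This is an inexpensive improvement, not a flaw in the trial's main question.

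**What to change.** Amend section 2.9.6 as follows.

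1. Compute intra-park anomalies among Tempest stations only. Do not pool the Campbell into the park-wide mean, or compare it with the corners, without adjustment for sensor type.
2. Base the immediate as well as the long-term pre/post temperature comparison on the fan-aspirated Campbell.
3. Use the baseline parallel data to estimate Tempest error by solar radiation and wind speed, restricted to units whose exposure is comparable with the Campbell's. Report corrected anomalies beside uncorrected ones.
4. Repeat the analysis for night-time hours and for overcast or breezy hours as a sensitivity check. True shade contrast also shrinks in those hours, so read this check alongside the correction and not alone. Do not interpret the solar-radiation correlation as an air-temperature effect unless it survives correction.

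No new measurement is needed: Table 2 lists solar radiation and wind speed for both station types, and the parallel data were collected at baseline. The cost is a little more analysis, calibration uncertainty from applying a centre-based fit to the corners, and probably smaller anomalies.
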